## Abstract

**Background:**

There is a growing demand globally for emergency department (ED) services. An increase in ED visits has resulted in overcrowding and longer waiting times. The triage process plays a crucial role in assessing and stratifying patients’ risks and ensuring that the critically ill promptly receive appropriate priority and emergency treatment. A substantial amount of research has been conducted on the use of machine learning tools to construct triage and risk prediction models; however, the black box nature of these models has limited their clinical application and interpretation.

**Objective:**

In this study, we plan to develop an innovative, dynamic, and interpretable System for Emergency Risk Triage (SERT) for risk stratification in the ED by leveraging large-scale electronic health records (EHRs) and machine learning.

**Methods:**

To achieve this objective, we will conduct a retrospective, single-center study based on a large, longitudinal data set obtained from the EHRs of the largest tertiary hospital in Singapore. Study outcomes include adverse events experienced by patients, such as the need for an intensive care unit and inpatient death. With preidentified candidate variables drawn from expert opinions and relevant literature, we will apply an interpretable machine learning–based AutoScore to develop 3 SERT scores. These 3 scores can be used at different times in the ED, that is, on arrival, during ED stay, and at admission. Furthermore, we will compare our novel SERT scores with established clinical scores and previously described black box machine learning models as baselines. Receiver operating characteristic analysis will be conducted on the testing cohorts for performance evaluation.

**Results:**

The study is currently being conducted. The extracted data indicate approximately 1.8 million ED visits by over 810,000 unique patients. Modelling results are expected to be published in 2022.

**Conclusions:**

The SERT scoring system proposed in this study will be unique and innovative because of its dynamic nature and modelling transparency. If successfully validated, our proposed solution will establish a standard for data processing and modelling by taking advantage of large-scale EHRs and interpretable machine learning tools.

**International Registered Report Identifier (IRRID):**

DERR1-10.2196/34201

## Introduction

### Background

Across the globe, there is increasing demand for emergency department (ED) services [1,2]. Increased ED visits have resulted in overcrowding and long waiting times [3-5]. Furthermore, adverse patient outcomes have been reported, such as mortality [6], poor patient satisfaction, and high costs [7,8]. As the first layer of emergency care in an ED, triage plays an essential role in assessing and stratifying patients’ risks and ensuring that the critically ill receive appropriate emergency treatment promptly [9].

The triage process is commonly conducted by medical staff based on their own clinical experience, the patients’ symptoms, and basic information obtained from patients during their presentation to the ED. To make this critical step more objective, triage systems have been introduced. Some examples of triage systems include the 5-level Emergency Severity Index [10] in the United States, the Australasian Triage Scale [11] in Australia, and the Patient Acuity Category Scale (PACS) [12] in Singapore. They are simple and easy to use but subjective and static. These scores are based on symptoms, but many critically ill patients may not have apparent symptoms when they arrive at the ED and their conditions deteriorate rapidly during their stay in the hospital. To address this limitation, more dynamic and accurate risk prediction tools are required for better patient monitoring throughout the ED journey [13].

In response to this gap of needs, researchers are interested in developing multivariable predictive models and clinical scores to identify patients in the ED at risk of adverse outcomes such as admission [14,15], death [16], cardiac arrests [17], and intensive care unit (ICU) admission [18]. Models such as these are primarily based on patient information, vital sign instability, changes in laboratory results, and administrative records. However, some parameters may appear similar between high-risk patients and other patients during an ED visit, making the prediction models less accurate.

Additional risk factors such as comorbidities, underlying chronic diseases, past hospitalization history, and other patient-related factors should be considered [19]. Furthermore, nonpatient factors are also integral components of patient care that can impact patient outcomes. Research has identified emergency boarding as a risk factor for mortality [6]. In addition, mortality rates were found to be higher for patients admitted during periods of high ED crowding regardless of their demographic characteristics, comorbidities, or primary diagnosis [20]. Changes in shift and high patient-to-nurse ratios have also been factors of concern [21].

In building predictive models, both traditional statistical methods and machine learning tools have been thoroughly investigated. Logistic regression is the most commonly used tool to construct multivariable prediction models [16,22,23]. In recent years, machine learning and artificial intelligence (AI) have gained popularity as tools for improving model performance. Fernandos et al [24] conducted an in-depth review of the current state of AI-based clinical decision support systems for triage. A recent study in the United States demonstrated the value of machine learning models for admission prediction in near real time [13].

While AI has proven successful in developing triage and prediction models, its solutions are often black box models, limiting model interpretation [25] and clinical adoption [26]. Consequently, efforts have been made to develop sparse predictive models by leveraging machine learning and conventional statistical analysis. Ustun and Rudin [27,28] proposed Supersparse Linear Integer Model–based methods for developing interpretable scoring systems. Xie et al [29] developed the interpretable machine learning–based AutoScore framework and used it to derive the score for emergency risk prediction to estimate the probability of mortality during an inpatient stay [30].

### Objective

By leveraging large-scale electronic health records (EHRs) and machine learning, we intend to create an innovative, dynamic, and interpretable System for Emergency Risk Triage (SERT) for risk stratification in the ED. This protocol describes the detailed data collection procedures, data manipulation, and predictive modelling to accomplish our goals. In particular, we will employ the AutoScore framework to construct a dynamic SERT for risk assessment at multiple decision points in the ED. Our solution will also be compared with traditional clinical triage tools and black box machine learning algorithms.

## Methods

### Study Setting

This is a large-scale, retrospective, single-center study conducted in Singapore. As a city-state in Southeast Asia with an approximately 5.4 million population, Singapore provides affordable health care through partial subsidies and co-payments. The study site, Singapore General Hospital, is Singapore’s largest and oldest tertiary referral hospital, with 1700 inpatient beds and over 30 clinical specialties. Each year, its ED sees more than 120,000 visits and admits 36,000 patients for inpatient care [16,31].

At public hospitals in Singapore, patients visiting EDs are triaged based on their symptoms according to the national PACS [32]. PACS-1 refers to patients who are seriously ill and require immediate medical care, PACS-2 refers to nonambulant patients who do not appear to be at risk of collapse, PACS-3 refers to ambulant patients, and PACS-4 refers to nonemergency cases. An initial triage is often recommended and used to identify patients who are more acutely ill and need immediate attention. As soon as resuscitation is required, the patient is taken directly to the resuscitation area. Otherwise, the patient will be directed either to a critical care area or a waiting area, depending on the patient’s condition.

### Study Cohort and Design

The flowchart of the entire project is shown in Figure 1. In the extracted data set, there are 3 primary identifiers: “*ED Case No,” “Admission Case No,”* and “*Patient ID,”* to represent the unique ED visit, the admission case, and the patient, respectively. Figure 2 illustrates how variables are constructed from and linked to these 3 identifiers. By consolidating the selected variables, a master data set will be created. Afterwards, the constructed master data set will be processed with outlier removal and missing value handling. The interpretable machine learning framework will then be implemented, and the models will be evaluated and compared with other baseline approaches, including traditional clinical scores, machine learning, and deep learning.

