### Data Cleaning and Preprocessing

Data extracted from EHRs may contain many erroneous entries, as the EHRs are designed for clinical use and not explicitly modified for research purposes. This results in a lot of noise, missing values, outliers, and duplicate or incorrect records due to system problems or clerical errors. These issues will be addressed in several ways. First, wholly duplicated entries will be removed. Second, if the vital signs or laboratory test results are outside the normal range, they are considered outliers. All outliers are marked as missing values and are handled by appropriate imputation methods (eg, the mean or median value imputation based on the training data set). Third, a descriptive analysis will be conducted to determine whether the overall percentage and number are within a reasonable range.

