### Variable Construction

Candidate variables have been identified based on expert opinions as well as relevant literature [18,30,34-36]. Moreover, we have sought input from clinicians and informaticians familiar with the raw data to determine which features are feasible to extract and construct from the sources. The general rationale is to include all ED-relevant variables of high quality. Therefore, irrelevant, repeated, or largely missing variables will be excluded. For time-series data (such as laboratory test results and vital signs), the first, last, and average measurements are extracted and constructed for each ED episode. Past health care utilization will be derived per the patient’s medical history.

Table 1 presents a list of high-level constructed variables. These variables are classified into 6 main categories depending on the time frame during which the variables could be collected: past medical history, ED triage, ED disposition, within the first 24 hours of inpatient stay, inpatient discharge, and after inpatient discharge. Variables of patient data include demographics, comorbidities, drug history, presenting vital signs, essential laboratory results, and treatments administered in the ED. There are also nonpatient variables such as ED waiting time from triage to consultation, ED boarding time (from consultation to ED disposition), patient load in the ED (number of other patients registered in the ED at that time), time of the day, and day of the week.

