### Outcomes

The clinical outcomes in this study include the following adverse events experienced by patients during their inpatient stay:

Admission: A hospital admission following an ED visit [37-39]. Each ED attendance is classified as admission or discharge according to the clinical decision made. As a result, patients who left before a decision could be made are excluded rather than considered discharged.Inpatient death: A clinically certified death of a patient admitted to the hospital and who died during the hospitalization.2/7/30-day mortality: A clinically certified death of an admitted patient that occurred 2/7/30 days after the ED visit regardless of the place of death.ICU transfer: Identified using the hospital’s admission, transfer, and discharge database. Whenever a patient had more than one transfer from ward to ICU, only the data before the first transfer were included.Cardiac arrest: Defined as the loss of a palpable pulse with attempted resuscitation in the ward.Prolonged hospital length of stay: Defined as 21 days or more for the hospital stay.

**Table 1 table1:** List of the high-level constructed variables in the master data set, along with their sources and categories.

Category	Subcategory	Source table	High-level variables extracted

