**Information collected at ED disposition**			
	ED vital signs	ED vital signs	Vital measurement frequency and major ED vital readings: pulse, respiration, fraction of inspired oxygen, SpO_2_, systolic BP, diastolic BP, temperature, pain level scale, Glasgow coma scale, alert (extracted from physical notes)
	ED laboratory	ED laboratory	Laboratory measurement frequency and major laboratory test results: potassium, creatinine, sodium, bicarbonate, albumin, creatine kinase-MB (mass), creatine kinase, prothrombin time, N-terminal pro–B-type natriuretic peptide, C-reactive protein
	ED consultation and treatment	ED consultation, ED treatment	Services provider, consultation waiting time, ED location, length of consultation, resuscitation, major emergency surgeries, pre-selected major ordering
	ED allergy	ED allergy	Major allergy types and reasons, severity
	ED disposition and diagnosis	ED disposition, ED diagnosis	Disposition type, major primary diagnosis, secondary diagnosis (eg, trauma)
	Outcomes	ED disposition, ED root table	Admissions, mortality within ED, direct transfer to ICU

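### The stated processing order removes outliers after the per-visit averages are built, so a recording error can hide in an average or cost the patient's valid readings; the cleaning section gives no order

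*Protocol article*

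**What the plan says.** The protocol article states one explicit sequence, in Study Cohort and Design. Variables are linked through three identifiers, and then "By consolidating the selected variables, a master data set will be created". The next sentence reads "Afterwards, the constructed master data set will be processed with outlier removal and missing value handling". Modelling follows.

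Variable Construction says what is built from repeated vital signs and laboratory results: "the first, last, and average measurements are extracted and constructed for each ED episode". The caption of Table 1 places such variables in the same data set: "List of the high-level constructed variables in the master data set, along with their sources and categories".

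Data Cleaning and Preprocessing, printed before Variable Construction, opens with the remark that "Data extracted from EHRs may contain many erroneous entries". Its rule is that "if the vital signs or laboratory test results are outside the normal range, they are considered outliers", and "All outliers are marked as missing values and are handled by appropriate imputation methods". It does not say whether the rule acts on single readings or on per-visit summaries.

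**The concern.** Taken together, the overview, Variable Construction and the Table 1 caption mean that the outlier filter acts on summaries. That has three consequences.

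- **Average, moderate error.** The wrong entry is diluted by the valid ones, and the average can lie inside the limits.
- **Average, gross error.** The average is flagged, and the whole value is set to missing although valid readings exist.
- **First or last value.** The wrong entry can still be seen and removed, but it is then imputed although the same patient may have a valid neighbouring reading.

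The cleaning section itself expects many erroneous entries from system faults and clerical slips. SERT-2 and SERT-3 draw on ED vital signs and laboratory results, so their candidate averages are exposed, as is any comparator fitted to the same summaries. What is at stake is avoidable measurement error and avoidable imputation in those predictors. The third cleaning step, a descriptive check of overall percentages and numbers, works in aggregate and would not reveal an in-range average that contains an error.

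**Working it through.** The plan gives no figure on this point, so there is none to reproduce. The order comes from the text set out above. The arithmetic only illustrates what the order does. Limits, readings and error rates below are assumptions, because the article states none of them.

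**Formula.** With k readings, of which k − 1 are valid at μ and one is an error e, the average is μ + (e − μ)/k. It stays within limits L to U when e lies between μ − k(μ − L) and μ + k(U − μ).

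**Narrow limits, as under a normal-range rule.** Assume pulse 60 to 100 and μ = 80. The window is 80 ± 20k.

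| k | Errors that pass in the average | Average with an entry of 8 | Average with an entry of 800 |
|---|---|---|---|
| 2 | 40 to 120 | 44.0, flagged | 440, flagged |
| 3 | 20 to 140 | 56.0, flagged | 320, flagged |
| 4 | 0 to 160 | 62.0, passes | 260, flagged |
| 6 | −40 to 200 | 68.0, passes | 200, flagged |
| 10 | −120 to 280 | 72.8, passes | 152, flagged |

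An error that itself lies between 60 and 100 escapes in either order. The loss due to the order is the rest of each window. Where the average is flagged, all k − 1 valid readings go with it. Had the raw entry been dropped first, the average would be 80 for every k.

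**A laboratory example.** Assume potassium limits of 3.5 to 5.0, valid results of 4.0 and an entry of 0.4. The average is 3.10 at k = 4 (flagged) and 3.55 at k = 8 (passes). Passing needs 4 − 3.6/k ≥ 3.5, so k ≥ 7.2. Masking here needs many repeats.

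**Wide limits, as under a data-error rule.** Assume pulse 20 to 250, systolic pressure 40 to 300, and k = 3.

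- Pulse, μ = 80: upper bound 80 + 3 × 170 = 590. A zero entry gives 160/3 = 53.3 and passes.
- Systolic, μ = 130: upper bound 130 + 3 × 170 = 640. A zero entry gives 260/3 = 86.7 and passes.

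Under the narrow pulse limits, both 53.3 and the average produced by 590, (160 + 590)/3 = 250, would be flagged. So the wider the limits, the more the order matters.

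**Frequency.** If 0.5% to 2% of readings are wrong, independently, then 1 − 0.995³ = 1.5% to 1 − 0.98³ = 5.9% of three-reading averages contain at least one error. This counts every such average, including those a later filter would catch, so it is not the rate of undetected error.

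**Reordering with the normal-range rule kept.** Suppose the readings 80, 80 and 180 are all true. Screening raw readings against 60 to 100 deletes 180 and leaves an average of 80 and a last value of 80, so the patient looks normal. Screening afterwards gives 340/3 = 113.3, flagged and set to missing. Neither is acceptable, and the first is harder to notice.

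**The case against.** The strongest reply is that the order is less fixed than the overview suggests. That paragraph is a short guide to Figure 1, which is not available here; nor is Figure 2. The cleaning section uses measurement-level wording and precedes Variable Construction, and Results reports that linking and cleaning are going on together. No section says that raw readings are screened before averaging, and none rules it out. This stands, and it is why the request is to reconcile two sections. It does not remove the point: the order in which sections are printed does not override an explicit statement of sequence.

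A reader might infer that an error is averaged in before any filter can see it. The documents do not support that. Gross errors, or errors among few readings, still push the average out of range, and first and last values are single readings that a later filter sees in full.

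A reader might also infer that the order is wrong whatever limits are used. That fails too: with the stated normal-range rule, reversing the order would remove genuine abnormal readings.

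The entry "Vital measurement frequency and major ED vital readings" in Table 1 might suggest that counts are contaminated as well. A mistyped reading is still a measurement taken, so counting it is defensible.

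Finally, AutoScore ranks variables, categorises continuous ones and keeps a sparse subset, and SERT-1 relies on simple triage measurements. The averages may not enter any final score. This stands and limits the severity.

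**Conclusion.** The concern holds in a limited form. The only explicit sequence in the article puts outlier removal after the summaries are built, and the cleaning section does not settle the level at which it acts. Followed as written, the order can hide moderate errors in averages, discard valid readings when the error is gross, and impute first or last values without need.

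The size of the effect on the scores cannot be stated, because error rates, limits and readings per visit are not given. The figures above rest on assumed values and show the mechanism only. Nothing in the documents shows that an outcome, a comparison or a conclusion would change, so a reading of this as a defect that must be fixed before the study can proceed is not supported. The severity is moderate.

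**What to change.** Amend Study Cohort and Design and reconcile it with Data Cleaning and Preprocessing, so that both state the same order:

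1. Remove duplicates and screen each raw reading for implausible values, using prespecified limits that identify data errors.
2. Build the first, last and average values from the valid readings that remain, so that the next valid reading takes the place of a removed first or last one.
3. Impute only where a visit has no valid reading left.

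Order and limits must change together. Reordering under the normal-range rule would delete true abnormal readings, and adopting wide data-error limits in the present order would widen the masking window. Measurement frequency may still count every non-duplicate measurement taken.

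The cost is script order, a set of limits and a sentence or two of text. Results says that linking and cleaning are still in progress, so nothing need be refitted now. Once the scores have been derived, the same correction would mean refitting them.

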**Figure 1 figure1:**
[figure not shown]
Flowchart of the study design. EHR: electronic health record.

**Figure 2 figure2:**
[figure not shown]
Illustration of the data linkage process of raw data tables through 3 primary identifiers. BP: blood pressure; ID: identification; ICD: International Classification of Diseases; ED: emergency department; ICU: intensive care unit; HDU: high dependency unit; SpO2: peripheral oxygen saturation; FiO2: fraction of inspired oxygen.

Singapore Health Services’ Centralized Institutional Review Board approved this study (CIRB Ref: 2021/2122), and a waiver of consent was granted to collect and analyze EHRs.

### Data Source and Extraction

Study subjects have been drawn from the hospital’s EHRs using the SingHealth-IHiS Electronic Health Intelligence System, which combines data from multiple clinical, operational, and finance data sources [33]. Before analysis, all data, including the 3 primary identifiers, have been de-identified to ensure that they are sufficiently anonymous. Records of deaths are obtained from the national death registry and are matched to specific patients in our database. Relevant variables are extracted from the beginning of the ED visits until the end of the patient’s journey. Moreover, patients’ medical histories are extracted and matched for each unique patient through *“Patient ID.”* The extracted data were saved in multiple CSV files for subsequent processing and analysis.

